### Study Population

The FASSETS study will take place in Marseille, which is the second largest city in France, and a significant proportion of its population has precarious living conditions [26]. The FASSETS study was developed in collaboration with the nongovernmental organization (NGO) AIDES and a Nigerian community NGO for women (The Truth), which provides HIV prevention and testing services to MWSWs.

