### Phase 2: Estimation of the Sample Size of the Hidden Population of MWSWs by Capture-Recapture

Population size estimation is a challenge because the MWSWs are hidden and difficult to reach. Hence, capture-recapture is recommended to estimate the size of the MWSW population in Marseille [27,28]. The estimation will be based on the following equation:

*N*=(*n*1×*n*2)/*m*

where *n*1 is the number of MWSWs who received a token (capture), *n*2 is the number of MWSWs included in the RDS study (recapture), and *m* is the number of participants common to both groups (MWSWs with a token). Tokens (safety whistle: a little emergency whistle with a flashlight) will be distributed over a period of 15 days by the NGOs and institutions but also directly to the MWSW network. Indeed, distribution of safety whistles will serve as a first “capture” and the RDS survey will serve as “recapture.” When participants visit the center for RDS enrollment, they will be asked if they had received a safety whistle; if they answer yes, the research team will ask them to identify the safety whistles from a group of photographs depicting different safety whistles. If the participants correctly identify the safety whistles from the photographs, they will be included as having received a safety whistle.

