### Phase 3: Representative Cohort Formation Through RDS and Follow-up

The inclusion criteria are being a cis- or transgender woman older than 18 years, self-reporting as having changed their sex for money or other resources during the past 12 months, having been born outside of France, living or working in the city of Marseille, and agreeing to participate in the study.

Numerous studies have demonstrated the effectiveness of RDS to engage adults in HIV research, particularly in stigmatized communities [29,30]. Initial RDS participants (ie, “seeds”) will be recruited for the study to achieve good representativeness in terms of the type of community or nationality, sex work (eg, indoor, outdoor, via the internet), place of residence in Marseille, and gender (cis- or transgender women). The prior qualitative study will make it possible to clearly define the characteristics of representativeness. Approximately 150 participants are expected to be enrolled in the cohort. At the beginning, participants will be offered 3 coupons. Participants who meet the eligibility criteria will be provided with a food coupon worth €10 (US $10.86) for completing each part of inclusion and follow-up (at months 3, 6, and 12), and another food coupon worth €10 (US $10.86) for each eligible and participating peer recruited. In addition, FASSETS study participants will be given public transport tickets, free condoms, and lubricating gel.

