### Training of Community Health Workers and Intervention Implementers

The CHWs will be members of the communities to which the recruited MWSWs belong. They will be able to improve recruitment, accurately monitor the correct understanding of the questionnaires, and conduct and ensure participation in empowerment, prevention, and screening interventions. They will provide information about PrEP and assist with care and follow-up for participants who wish to receive the treatment. They will be uniformly trained to conduct the survey using a structured interview. All actions (type, date, and public) taken by the CHWs with MWSW participants (eg, access to care, prevention, and assistance in accessing social insurance) will be also collected.

The CHWs will be responsible for health education and individual and collective empowerment actions. They will receive rigorous prejob training and assessment, which include PrEP use and sexual health prevention and care, by caregivers (infectious disease physicians) and nationally recognized community-based NGOs working in the field of HIV prevention (including AIDES, Planning familial, and COREVIH [COordination REgionale de lute contre le Virus de l’Immunodéficience Humaine]). The training program will be conducted with the entire CHW group and will also include individualized follow-up. All CHWs will have a discussion platform via a social network to obtain real-time responses from physicians. Information or prevention tools, adapted to the MWSW populations, will be made available to the CHWs by the NGO’s partners. Posttraining mentorship, supervision, and monitoring with regular training will take place every 3 months by the investigating physicians. CHWs’ course evaluation feedback and posttraining monitoring visits will be provided by the study coordinator. Finally, a follow-up and psychological support will be set up to support the CHWs in their work with this vulnerable population.

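### The population-size formula uses raw counts that include the seeds, and tokens travel the same network as the coupons, so dependence between capture and recapture is likely and left uncorrected

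*Protocol article*

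**What the plan says.** The article's Phase 2 section commits to a two-sample estimator: "The estimation will be based on the following equation", namely N = n1×n2/m. Of n1 it says that it "is the number of MWSWs who received a token (capture", and of n2 that it "is the number of MWSWs included in the RDS study (recapture". The overlap m is the number of women in both groups. The tokens are safety whistles, handed out over 15 days "by the NGOs and institutions but also directly to the MWSW network". A woman counts in m only if she reports having received one and then picks it out from photographs.

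The Phase 3 section treats seeds as the first RDS participants. They "will be recruited for the study to achieve good representativeness in terms of the type of community or nationality" and other traits. Later participants arrive on peer coupons, three per woman. On size: "Approximately 150 participants are expected to be enrolled in the cohort".

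The Study Population section names as partners AIDES and "a Nigerian community NGO for women (The Truth), which provides HIV prevention and testing services to MWSWs". The section on community-based participatory research says that the study grew up around these two organisations. Community health workers (CHWs) come from the women's own communities, and their training section says: "They will be able to improve recruitment". The Data Collection section has network size recorded for RDS weighting, but the equation for N contains no weight.

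Nothing in the article takes seeds out of n2 or m, separates the token routes, or allows for dependence.

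**The concern.** With two lists, n1×n2/m recovers the population size only if holding a token does not change a woman's chance of entering the RDS sample. Two stated features work against that.

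- **Shared route.** Tokens are sent into the women's network, and coupons then travel along that network. A well-connected woman is more likely to be reached by both. Contact with the partner organisations may act in the same way.
- **Seeds.** Under the stated definitions they count as recaptured, although the study selected them. If the selection favours women who already hold tokens, m is inflated.

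The size of this population is the second objective in the Introduction and the Phase 2 key outcome, and the abstract's conclusions promise firm evidence on it. The women most easily missed by both lists are those with few ties, whom the method is meant to bring into the count.

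**Working it through.** **Inputs.** From the article: the equation, the definitions of n1, n2 and m, and n2 of about 150. The article gives no N, n1, m, number of seeds or token share among seeds, so there is no stated figure to reproduce. Assumed for illustration: true N = 1000, n1 between 150 and 500, and 5 or 10 seeds.

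**1. Dependence.** Let a token holder be RR times as likely as another woman to enter RDS. Then the expected m/n2 = RR·n1/(RR·n1 + N − n1), and the formula returns

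N̂ = (N − n1 + RR·n1)/RR.

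For n1 = 300 and RR = 1.5: (700 + 450)/1.5 = 767.

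| RR | n1 = 150 | n1 = 300 | n1 = 500 |
|---|---|---|---|
| 1 | 1000 | 1000 | 1000 |
| 1.25 | 830 | 860 | 900 |
| 1.5 | 717 | 767 | 833 |
| 2 | 575 | 650 | 750 |

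**2. Seeds alone.** Let s seeds all hold tokens and the other 150 − s women be independent of token status. Then m = (150 − s)·n1/N + s.

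- n1 = 200, s = 10: m = 140×0.2 + 10 = 38, and N̂ = 200×150/38 = 789.
- n1 = 300, s = 10: m = 140×0.3 + 10 = 52, and N̂ = 300×150/52 = 865.
- n1 = 300, s = 5: m = 145×0.3 + 5 = 48.5, and N̂ = 300×150/48.5 = 928.
- Seeds left out, n1 = 200: n2 = 140, m = 28, and N̂ = 200×140/28 = 1000.
- Seeds tokened at the population rate (30% for n1 = 300): m = 45 and N̂ = 1000, with or without the seeds.

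**3. Errors in the other direction.** If only a share r of token holders recall and identify the whistle, m shrinks to r·m and N̂ rises to N/r: 1111 at 90% and 1250 at 80%. If 15% of tokened women leave and are replaced before RDS, N̂ = 1000/0.85 = 1176.

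**4. Both together.** RR = 1.5 with 80% recall gives 717/0.8 = 896, 767/0.8 = 958 and 833/0.8 = 1042 for n1 = 150, 300 and 500. The net error changes sign within this range. Recall of 72%, 77% or 83%, respectively, would exactly cancel RR = 1.5.

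**5. Precision lost by excluding seeds.** The simple standard error is √[n1·n2·(n1 − m)(n2 − m)/m³]. For n1 = 300, n2 = 150, m = 45 it is √(300×150×255×105/45³) = 115. With ten seeds out (n2 = 140, m = 42) it is √(300×140×258×98/42³) = 120. This ignores any RDS design effect.

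**The case against.** The strongest reply has four parts.

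- **The link through the organisations is not stated.** A reader might infer that the partner NGOs supply the RDS sample, or that the women's network hands out the tokens. The article says neither. It does not give the source of the seeds, it describes the network as receiving tokens, and it says only that CHWs help recruitment. This stands: the NGO link is a reasonable inference, not a fact of the plan. The shared network and the counting of seeds are stated.
- **The direction is open.** A reader might infer that N must come out too low. Steps 3 and 4 show otherwise, since the photograph check and departures before enrolment can offset or reverse the effect. This stands too. But an opposite error of unknown size does not cure dependence; it leaves two uncontrolled biases.
- **The seed figures are a worst case.** Seeds are sought for diversity of community, residence, gender and type of sex work, and nothing says that they hold tokens more often than other women. This also stands. Yet whether they do is unknown, and leaving them out removes the question.
- **This may be detail for an analysis plan.** The article condenses a longer document, and network size is collected for weighting. That would excuse silence, but here the estimator, the membership of n2 and m, and the token routes are written out, and it is those stated rules that cause the difficulty.

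**Conclusion.** The concern holds in a limited form. The plan applies an estimator that needs independent captures to raw counts that include the seeds, and it sends tokens into the network that the coupons then use. Positive dependence is likely and, taken alone, biases N downward.

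Under the assumed N = 1000 and n2 = 150, a modest RR of 1.5 costs 17% to 28% (N̂ of 833 to 717). Ten fully tokened seeds cost 21% at n1 = 200 or 13% at n1 = 300, and seeds tokened at the population rate cost nothing. Apart from n2, every figure here is an assumption. Neither the true size of the bias nor its net sign can be read from the article. For that reason N should not be presented as a lower bound, tempting as that label is.

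**What to change.** 1. Define n2 as the women enrolled on a peer's coupon, and m as those among them who identify the token. Seeds, and any woman brought in directly by a CHW or NGO, stay in the cohort but out of both counts.
2. Estimate the token share p = m/n2 with the network-size weights already being collected, and use N = n1/p. This addresses dependence that arises from being well connected; it does not remove dependence through contact with the same organisations.
3. Record how each woman got her token and her coupon.
4. Report N with a sensitivity range. Rearranging step 1 of the working gives N(RR) = n1·[1 + RR·(1 − p)/p]. For example, n1 = 300 and p = 450/1150 give 767 at RR = 1, 883 at 1.25 and 1000 at 1.5. Imperfect recall r enters by replacing p with p/r.

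Two other changes may suggest themselves and are better avoided. Dropping the direct-to-network route would concentrate tokens among women reached by the organisations and could strengthen that dependence. Estimating N by community and type of work would split an m of perhaps 30 to 45 into sparse cells.

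**Cost.** Revised definitions, one or two items on the enrolment record and a short sensitivity table. n2 loses a few women; with ten seeds out, the standard error goes from 115 to 120 in the example. Recruitment began on March 1, 2022, so tokens may already have been distributed. Items 1, 2 and 4 can still be applied at analysis if coupon records were kept; item 3 would then depend on what was recorded or can still be asked at follow-up.

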### Phase 3: Representative Cohort Formation Through RDS and Follow-up

The inclusion criteria are being a cis- or transgender woman older than 18 years, self-reporting as having changed their sex for money or other resources during the past 12 months, having been born outside of France, living or working in the city of Marseille, and agreeing to participate in the study.

Numerous studies have demonstrated the effectiveness of RDS to engage adults in HIV research, particularly in stigmatized communities [29,30]. Initial RDS participants (ie, “seeds”) will be recruited for the study to achieve good representativeness in terms of the type of community or nationality, sex work (eg, indoor, outdoor, via the internet), place of residence in Marseille, and gender (cis- or transgender women). The prior qualitative study will make it possible to clearly define the characteristics of representativeness. Approximately 150 participants are expected to be enrolled in the cohort. At the beginning, participants will be offered 3 coupons. Participants who meet the eligibility criteria will be provided with a food coupon worth €10 (US $10.86) for completing each part of inclusion and follow-up (at months 3, 6, and 12), and another food coupon worth €10 (US $10.86) for each eligible and participating peer recruited. In addition, FASSETS study participants will be given public transport tickets, free condoms, and lubricating gel.

### Phase 4: FASSETS Community Empowerment Intervention and Follow-up Program

#### Empowerment Framework

There are many definitions of participant empowerment in the literature [31]. In this study, empowerment intervention will be defined as a process by which MWSWs take collective action to achieve the most effective SRH outcomes and address social and structural barriers to their health and human rights [32]. Most effective SRH effects have been defined in accordance with national and international guidelines [33,34]. The main outcomes are related to a decrease in the number of sexually transmitted infections, unintended pregnancy and abortion, sexual violence, and an increase in the access to comprehensive, good-quality information about sex and sexuality and the ability to access sexual health care. The main goal is to mainstream migrant health access to include people-centered health services. Community empowerment programs conducted in many countries to reduce HIV risk among WSWs have previously proven their effectiveness [35]. In order to evaluate empowerment, 5 specific principles will be used, including improvement, democratic participation, community knowledge, evidence-based strategies, and capacity building [36].

#### Participant and Public Involvement

CHWs and peer workers were involved in the design of the structures survey, with special attention paid to the terms and methods of communication used during participant interviews.

Participants will be involved in the intervention phase in the design of individual and collective empowerment actions. CHWs will be involved in the dissemination plans of this study by communicating in public conferences and workshops with local and nationwide actors in the field.

#### Community-Based Participatory Research

Community-based participatory research is an approach to research that involves a collective, reflective, and systematic study in which researcher and community stakeholders engage in all steps of the research process with the goal of improving practice [37]. This approach to research is recognized as particularly useful when working with populations that experience marginalization—as is the case for MWSWs—because it supports the sharing of control over individual and group health and social conditions [37,38]. The FASSETS study was initially developed around 2 community NGOs, AIDES and The Truth, which provide SRH community interventions for MWSWs. In accordance with community-based participatory research principles, this study will involve partnership building, regular exchange among partners and community NGOs, and experience sharing among the researchers, CHW staff, and the MWSW community. A community-based participatory research approach could mitigate the intersecting forms of marginalization faced by MWSWs. Indeed, a participatory approach is of particular relevance in health equity research, in which cultural and socioeconomic differences among the community, health care givers, and researchers potentially impede the identification of problems and discovery of their causes [39]. Partnering with the community will by no means eliminate this barrier during the evaluation but can enhance understanding and increase insight into the social and physical conditions as well as policy environments that are impacting the health of the community [39,40]. During the program and results dissemination, researchers, community participants, partner NGOs, and CHWs could also participate in increasing the use of social and health service usage by MWSWs and in advocacy to improve the overall living conditions of MWSWs.

### Implementation Study

The term “implementation research” describes the scientific study of the process used in the implementation of an initiative as well as the contextual factors that affect these processes [41]. This study aims to address the factors affecting the implementation of PrEP among MWSWs (such as health literacy, poverty, access to health, or traditional beliefs), the processes of implementation themselves (proposal, distribution, and follow-up of PrEP), and the outcome of the implementation under study. Indeed, the FASSETS study should be aligned with MWSWs’ needs and respond to the particularities of different communities. The study will be conducted in a real-world setting and will consider context and other factors that influence implementation. A qualitative study will help understand and document the PrEP empowerment actions in the FASSETS cohort and to describe the community mediation implementation with its positive or negative impact on MWSWs and their needs.

### Field Implementation

The FASSETS intervention will take place at a center for enrollment and empowerment (Figure 2). The health care and social service network for MWSWs has already been mapped (Figure 2). Some NGOs and CHWs of the study are mobile and will visit some prostitution sites.

After inclusion, participants will be offered to be followed up at least every 3 months by CHWs, either in the mobile or fixed area, on the basis of their preference. Participants will also have access to health screening centers and other institutions or NGOs any time they need them, in addition to planned individual or collective meetings.

**Figure 2 figure2:**
[figure not shown]
Mapping of the sexual health and social care and support network for migrant sex workers in Marseille. PrEP: pre-exposure prophylaxis; NGO: nongovernmental organization; STI: sexually transmitted infection.

### Training of Community Health Workers and Intervention Implementers

The CHWs will be members of the communities to which the recruited MWSWs belong. They will be able to improve recruitment, accurately monitor the correct understanding of the questionnaires, and conduct and ensure participation in empowerment, prevention, and screening interventions. They will provide information about PrEP and assist with care and follow-up for participants who wish to receive the treatment. They will be uniformly trained to conduct the survey using a structured interview. All actions (type, date, and public) taken by the CHWs with MWSW participants (eg, access to care, prevention, and assistance in accessing social insurance) will be also collected.

The CHWs will be responsible for health education and individual and collective empowerment actions. They will receive rigorous prejob training and assessment, which include PrEP use and sexual health prevention and care, by caregivers (infectious disease physicians) and nationally recognized community-based NGOs working in the field of HIV prevention (including AIDES, Planning familial, and COREVIH [COordination REgionale de lute contre le Virus de l’Immunodéficience Humaine]). The training program will be conducted with the entire CHW group and will also include individualized follow-up. All CHWs will have a discussion platform via a social network to obtain real-time responses from physicians. Information or prevention tools, adapted to the MWSW populations, will be made available to the CHWs by the NGO’s partners. Posttraining mentorship, supervision, and monitoring with regular training will take place every 3 months by the investigating physicians. CHWs’ course evaluation feedback and posttraining monitoring visits will be provided by the study coordinator. Finally, a follow-up and psychological support will be set up to support the CHWs in their work with this vulnerable population.

### Data Collection

Upon enrollment and at months 3, 6, and 12, participants will be asked to complete a structured survey administered by a CHW. The survey will include questions regarding network size for RDS weighting. These will include questions about the token given at the time of data capture. Individual data including sociodemographic characteristics; sexual practices; knowledge and behavior; HIV testing history; medical history; PrEP knowledge, adherence, and compliance; contraception; drug and alcohol use; mental health (including Perceived Stress Scale-10 scores); quality of life; literacy; social support; being subjected to racism; stigmatization or violence during the past 12 months; and mobility will be collected. Other more structural determinants will be collected as follows: residence permits, health insurance, housing conditions, and food security (Table 1). Indeed, such structural determinants are previously described to have a significant impact on health care access among sex workers [42]. The semistructured questionnaire will explore the barriers and levers to accessing PrEP among MWSWs. The instrument or interview guide will attempt to understand how PrEP fits into women’s needs, care pathways, and mobility. Representation of MWSWs’ PrEP uptake among caregivers and which mechanisms are (or are not) implemented by social institutions to facilitate access to prevention and care for MWSWs (Table 1).

Type, objective, and number of actions of mediation in terms of prevention, support, or access to health care or social services will be self-reported by CHWs.

CHWs will use encrypted and secure survey software to report the MWSWs’ responses to the questionnaires and to monitor their actions of mediation. All electronic questionnaires will be forwarded to a database that is managed and hosted by SESSTIM (Inserm laboratory in Marseille). Each staff member will have a secure individual account.

Databases of all NGOs and institutional screening and PrEP centers of Marseille will be retrospectively analyzed to describe the HIV status and to assess PrEP characteristics among migrants and women in Marseille.

**Table 1 table1:** Data collection tools and timing.

Method	Timing	Population	Data collected
Questionnaire	4 rounds: months 0, 3, 6, and 12	Randomized migrant woman sex worker cohort in Marseille	Sociodemographic data, knowledge of sexual health, results of tests for sexually transmitted diseases, medical treatment including pre-exposure prophylaxis (PrEP), retention time in care, health care pathway, residence permit, health insurance coverage, housing conditions, and food security
Questionnaire	Continuous	Community health workers	Type, number, and objective of actions
Semistructured interviews and focus groups	Continuous from September 2021 through January 2022	Migrant women sex workers	Perception of PrEP and sexual health, qualitative explanation of possible empowerment mechanisms, health needs, and care pathway
Semistructured interviews	Continuous from September 2021 through January 2022	Nongovernmental organizations (NGOs) and institutions in charge of the sexual health of sex workers in Marseille	Perception of PrEP and sexual health in migrant women sex workers, identification of available empowerment resources for migrant women, and health care offer
Observation	Continuous	NGOs and institutions in charge of the sexual health of sex workers and migrants in local and international territories	Social history of public sexual health strategies among migrant women sex workers

